#### Physiological Assessments

Physiological assessments are summarized in Table 2. The APGAR [70] score is derived after birth to give a measure of the baby's overall health. Research assistants, nurture specialists, study coordinators, and study investigators collect these measures. Blood is collected by the medical staff using the heel stick method at times determined by the clinical protocols used in our NICU. A portion of this blood is retained for use in our study. EEG is recorded using a 128-electrode net and data acquisition system (EGI, Inc, Eugene, Oregon). When possible, a one hour recording of high density EEG is obtained during sleep at two times during the NICU stay between 34 and 36 weeks PMA and after discharge at 39 to 42 weeks. ECG and respiration are also recorded during these sessions. Recordings are obtained within 30 minutes of feeding and are conducted between 11 am and 4 pm. EEG and ECG are collected at 1000 samples/sec and respiration (chest impedance belt) at 50 samples/sec. Throughout the recording sessions, RAs assign sleep state codes (quiet sleep, active sleep, indeterminate, awake, cry) once each minute, based on behavioral criteria previously shown appropriate for prematurely born infants [71]. ECG records are processed using techniques our group has developed and published previously [72,73]. These analyses provide estimates of heart rate and heart rate variability indices of autonomic regulation for each sleep state. EEG data are processed to obtain spatially-dependent measures of wave amplitude (power) at specific frequencies for each spatial location as well as measures of functional connectivity (coherence) between electrode locations [73].

Heart rate variability (HRV) will be assessed to provide indices of autonomic control during the three EEG assessments completed in the NICU and during the follow ups at 4, 12 and 24 months CA. HRV refers to rhythmic and predictable time-related changes in interbeat intervals (IBIs). HRV can be seen in a continuous recording of IBIs (or heart rate) over time. It is best seen while the infant is breathing normally or breathing at a paced rate within a normal physiological range. Heart rate variability is a measure of autonomic function. Respiratory rate and variability are measured at the same times using a respiratory belt and body temperature is measured employing a temperature probe taped to the flank of the baby. These measures provide an overall indication of the infant's autonomic function.

As a component of the mother-infant interaction assessments conducted at 4 and 12 months CA (see below), salivary cortisol levels are measured at four times during each session (and additionally at 18 and 24 months CA). Previous research has shown that neuroendocrine responses measured via cortisol in pre-term infants are a robust marker of stress reactivity [74]. These measures provide physiological indices of how the infants respond to a social interaction stressor. In addition, breastmilk, saliva (mother and infant), and infant blood for peptides/cytokines/gene arrays are collected and stool is sampled to assess the gut microbiome and markers of inflammation.

##### Face-to-Face Interactions

At the 4 and 12 month CA follow-up visits to the clinic, a split-screen filming session is conducted following protocols developed in the laboratory of Beebe and Jaffe [52]. These videotapes are subsequently analyzed, by team members 'blind' to the dyads' group assignments, in order to assess mother-infant face-to-face communicative competence, sensitivity of maternal caregiving and mother and infant physiological capacity to cope with a stressor. The ~60 min 4-month protocol (Figure 3) consists of the following segments: (1) obtaining mother's consent, (2) mother-infant play, (3) stranger-infant play, (4) diaper change, (5) the Still Face protocol in which mothers assume an expressionless face for two minutes [77], (6) administration of the maternal questionnaires. Cortisol is measured at 3, 12, 18 and 24 months CA (Table 2). Data from these sessions are used to determine mother and infant social competence during spontaneous face-to-face interactions and changes in interactions in response to the Still Face probe. Primary measures are: infant gaze aversion, mother-infant gaze coordination, infant distress, maternal interaction style (affectionate vs. intrusive), and responses of mothers and infants to gaze aversion.

**Figure 3 F3:**

**Four-month follow-up visit time-line**. The ~60 min protocol consists of: (1) consent, (2) mother-infant play, (3) stranger-infant play (4) diaper change, (4) Still-Face paradigm, (5) parental questionnaires. Cortisol (c; "red circle") is measured at 4 times: consent, ~15 min after mother-infant play (before diaper change), 15 min after still-face (~min 49), and 30 min after still-face (~min 64). Abbreviations: c "red circle", cortisol; HR, heart rate; HRV, heart rate variability; M/I, mother-infant; S/I, stranger/infant.

#### Assessments of NICU Activities

Ascertainment of attendance and the frequency and/or time spent engaged in key aspects of the FNI are obtained from maternal self-report forms. These forms are filled out after each visit to NICU. The mother is asked to enter information about the start and stop times of each of her visits to the NICU and to estimate the amount of time or number of times she engaged in various types of interactions with her infant. A similar schedule of questionnaires is given to the SC group mothers, but without questions that pertain only to the FNI group (e.g., odor cloth exchange, *Calming Cycle*). Documentation of the extent to which the SC group engages in KC, holding, and feeding will provide some information about potential cross-contamination between the groups.

Research nurses keep logs of intervention activities and their duration while facilitating the intervention with FNI mothers. Additionally, mothers in both groups complete logs of weekly nurture activities. It is possible that kangaroo care is done in the SC group and we request that the mothers log this information. It is important to note that calming touch, vocal soothing, and odor-cloth exchange are not aspects of SC in the NICU.

### Primary and Secondary Outcome Measures

The primary outcome measures assess the neurodevelopment and physiological functioning of the premature infant from birth through 24 months CA as summarized in Table 2. Primary outcome measures include: infant brain activity at term, as measured by EEG; infant neurobehavioral function from response to NNNS [62], preschool language scale [78], ASQ [68] and at 18 months CA by Bayley-III Scale [69], and the stress response at 4 months CA in infants, as measured by heart rate variability (HRV) and cortisol levels.

Our secondary outcome measures assess the co-regulation of the mother and the infant. Mother's mood, temperament and attachment will be assessed using: STAI, CES-D, BIS-BAS, ATQ, PSI, MSES, and the AAI. The infant's mood and temperament will be assessed using: BITSEA, IBQ-R, EITQ and CBCL. Mother-infant interactions and attachment will be assessed through scoring video recordings. Mother-infant stress responses will be evaluated by cortisol level assessment and autonomic function recordings (HRV, respiratory rate, body temperature). A mother's nurturing ability will be assessed by self-report and NS rating of nurturing abilities and the duration of nurturing behaviors as revealed by the Nurture Time Daily Log, the Maternal Nurture & Family Support Meeting, the Home Nurture Questionnaire and the NSSQ. An additional secondary outcome is the degree to which FNI may improve family support, which is assessed with the Mom's Support Circle worksheet. We will also collect data for an additional secondary, exploratory outcome-the effect of FNI versus SC upon peptide/cytokine/gene expression in the blood and/or breastmilk and upon the gut microbiome.

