## Methods and Design

FNI is a randomized controlled trial designed to determine the short- and long-term physiological and behavioral effects of a family nurture intervention on preterm infant development. The intervention takes place over the course of the NICU stay. FNI is designed to help the mother and her preterm infant engage in interactive biologically important activities and behaviors that enhance the maternally-mediated sensory experiences of preterm infants, as well as the infant-mediated sensory experiences of the mother. Extended family members are also engaged and encouraged to adopt both a supportive and supplementary role in the process. Our primary hypotheses are that the FNI group will have increased infant brain activity as assessed by electroencephalogram (EEG) power and better basic neurobehavioral function close to term and at 18 months CA as compared to the Standard Care (SC; described below) group. Our secondary hypotheses are that the FNI group will have decreased stress responses in mother and infant at four months CA, fewer maternal anxiety and depressive symptoms after discharge from the NICU, as well as better maternal attachment and support systems as compared with the SC group. In addition to the aforementioned measures, we are also collecting samples of infant blood, breastmilk and stool samples from mother and infant.

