**Mother**					
**Cortisol **[**89**]	4 months	Median = 2.4	0.45	.40	186
		(IQR: 1.6-4.1)			
**CES-D **[**53**]	4 months	10.24(9.67)[90]	5.0	.52	120
		19.8 (11.1)[91]		.45	158

A power analysis was conducted to determine the sample size needed to ensure statistical power of (1-*β*) = .80.

*Non-optimal reflexes. Illustrative of the 13 NNNS subscales. Citation for the reference population is the same as that for all Outcome Measures except CES-D. Abbreviations: Bayley-III, Bayley Scales of Infant Development, III; CES-D, Center for Epidemiological Studies Depression Scale; HRV, heart rate variability; NNNS, NICU Network Neurobehavioral Scale; PMA, post-menstrual age of the infant.

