#### Neurobehavioral Assessments of Infants

At regular time points during the study, the neurobehavioral status of the infants is assessed using either standardized examinations conducted by research team members who are 'blind' to the infants' group assignments or through maternal questionnaires (Table 2). The first of these is the NICU Network Neurobehavioral Scale, NNNS [62], which is conducted twice, once at 36 weeks (± 1 week) PMA and again at 40 weeks (± 1 week). This assessment has several domains that provide information about the infant's neurodevelopmental status. The test measures neurological reflexes, body tone and motor maturity. It also measures the infant's orientation to and engagement with social and non-social stimuli, the lability of the infant's activity and states, and the infant's consolability. The stress/abstinence scale, originally formulated for prenatally drug-exposed infants, includes physiological, autonomic, skin, CNS, visual and gastrointestinal markers [63].

In addition to these blind assessments, mothers provide a wide range of information about their infant's development through questionnaires. At 4, 12, 18, and 24 months CA information about infant temperament is obtained using the Early Infancy Temperament Questionnaire, EITQ [64] and the Infant Behavior Questionnaire, IBQ-R [65]. Social-emotional problems of the infants are assessed by the Brief Infant-Toddler Social and Emotional Assessment, BITSEA [66] at 4, 12, 18, and 24 months CA, and at 18, 24 months CA by the Child Behavior Checklist, CBCL [67]. The mother also provides information about possible developmental delays by filling out the Ages and Stages Questionnaire, ASQ [68], at 4, 12, 18 and 24 months CA.

At 18 and 24 months CA, infants are administered the Bayley Scales of Infant and Toddler Development, Bayley III [69] consisting of four subscales: Cognitive, Language (receptive/expressive), Motor (fine/gross) and Social-Emotional. These filmed assessments, made by research staff 'blind' to infant group assignment, provide information about the neurobehavioral status of the child and whether there are significant delays in key domains of motor, language, and cognitive development.

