### Planned analyses

Descriptive statistics will be derived for all predictor and outcome variables. Family socio-demographic characteristics are not expected to differ by study group, but significance tests will be conducted to confirm the success of the randomization process. Outcomes for the two study groups including infant EEG measures, stress and development, and maternal stress and depression will be compared at each measurement interval (intake, term, 4, 12, 18, and 24 months CA) using independent t-tests for differences between means for continuous data and chi-squared tests for differences between proportions for categorical data. The Bonferroni correction will be applied to account for multiple testing. Longitudinal analyses assessing differences over time will be conducted using repeated measures ANOVA for continuous data and Kruskal-Wallace or Friedman's adaptation of this test for non-parametric data. Generalized linear models will be used to assess the variability in infant development, as measured by Bayley-III Scales at 18 months CA. This variability is explained by repeated maternal and infant psychological and neurological factors after controlling for baseline family socio-demographic characteristics.

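### Primary outcomes are named as whole instruments and the Bonferroni family is undefined, so neither the error rate nor the power of the primary analysis is fixed

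*Protocol article*

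**What the plan says.** All places are in the protocol article.

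- **Primary and Secondary Outcome Measures:** "Primary outcome measures include: infant brain activity at term, as measured by EEG; infant neurobehavioral function from response to NNNS". The list continues with the preschool language scale, ASQ and Bayley-III ("and at 18 months CA by Bayley-III Scale"), then infant HRV and cortisol at 4 months. That is seven instruments or markers, with no score named for any of them. ASQ has no visit here; Table 2 gives four.
- **Methods and Design:** the primary hypotheses are "increased infant brain activity as assessed by electroencephalogram (EEG) power and better basic neurobehavioral function close to term and at 18 months CA". This settles on EEG power and gives approximate ages, but no band, region or scale.
- **Neurobehavioral Assessments of Infants:** the Bayley-III is described as "consisting of four subscales: Cognitive, Language (receptive/expressive), Motor (fine/gross) and Social-Emotional".
- **Physiological Assessments:** the 128-electrode EEG yields "spatially-dependent measures of wave amplitude (power) at specific frequencies for each spatial location as well as measures of functional connectivity (coherence" between electrodes.
- **Table 1:** one mean and SD per instrument. The powered NNNS score is non-optimal reflexes, and the footnote calls it "Illustrative of the 13 NNNS subscales".
- **Planned analyses:** group comparisons at each measurement interval, repeated measures ANOVA over time, and one sentence on multiplicity: "The Bonferroni correction will be applied to account for multiple testing".

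**The concern.** A primary outcome has to say which number decides. Here the NNNS could be judged on any of 13 scores, the Bayley-III on any of four, and EEG power on an uncounted set of bands and locations. The footnote to Table 1 declines to nominate even the one NNNS score that was powered. The plan also does not say whether the comparison at a visit or the repeated measures analysis decides.

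A Bonferroni correction controls error only once its number of tests is fixed. With the family left open, two analysts who both follow the text could use different thresholds and different scores and reach opposite conclusions about neurobehaviour or brain activity. The commitment under Potential limitations that reporting will not be selective could not be checked against named scores.

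**Working it through.** **1. Reproduce Table 1.** Two-sample t-test, two-sided alpha .05, power .80, 1:1, using Table 1's differences and SDs.

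| Outcome | Difference / SD | Stated N | Recomputed N |
|---|---|---|---|
| EEG | 0.2 / 0.434 = 0.461 | 150 | 150 |
| NNNS (non-optimal reflexes) | 1.0 / 1.73 = 0.578 | 96 | 96 |
| HRV | 0.5 / 1.10 = 0.455 | 154 | 154 |
| Bayley-III | 6.0 / 14 = 0.429 | 174 | 174 |

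The match is exact, so the sample size rests on one unadjusted .05 test per instrument. (The Bayley-III effect size is printed as .41; the stated N corresponds to 6/14 = .43, which I use below.)

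**2. Retained sample.** 260 × (1 − 0.40) = 156, or 78 per group.

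**3. Reading A: Bonferroni across instruments only.** This is an assumed reading, .05/4 = .0125 for the four infant rows of Table 1. Within an instrument with m scores sharing a common correlation ρ, the chance of at least one false positive at level a is

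F(m, a, ρ) = 1 − ∫ φ(x) [Φ((c − √ρ x)/√(1−ρ)) − Φ((−c − √ρ x)/√(1−ρ))]^m dx, where c = Φ⁻¹(1 − a/2).

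The documents give no correlations, so I take ρ = 0.5 with a range of 0.8 to 0.3, and independence between instruments. With NNNS m = 13, Bayley-III m = 4, HRV m = 1 and a single EEG measure:

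| ρ | F for NNNS | F for Bayley-III | Joint rate = 1 − (1−F_NNNS)(1−F_Bayley)(0.9875)² |
|---|---|---|---|
| 0.8 | 0.060 | 0.032 | 0.11 |
| 0.5 | 0.107 | 0.043 | 0.17 |
| 0.3 | 0.132 | 0.047 | 0.19 |

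With ten EEG measures (also an assumption) the joint rate is 0.23, range 0.15 to 0.27.

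**4. Reading B: Bonferroni over every score.** With 13 + 4 + 1 + 10 = 28 scores tested at .05/28 = .0018, the joint rate is 0.041 (0.027 to 0.046), so error is controlled. Power for Table 1's own differences at 156 retained:

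| Alpha | EEG | NNNS | Bayley-III |
|---|---|---|---|
| .05 | 82% | 95% | 76% |
| .05/3 = .0167 | 68% | 88% | 60% |
| .05/7 = .0071 | 56% | 81% | 48% |
| .05/13 = .0038 | 48% | 75% | 40% |
| .05/28 = .0018 | 39% | 67% | 31% |

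The .05/7 row is what results if all seven listed outcomes stay primary with one score each. At .05/3, the totals needed for 80% power are 202, 130 and 232, against 150, 96 and 174 in Table 1.

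**The case against.** The strongest reply is that the plan does promise a correction. A reader might infer uncorrected error rates at ρ = 0.5 of about 0.33 for 13 NNNS scores and 0.16 for four Bayley-III scores, each tested at .05. The documents do not support this, because the Bonferroni sentence follows directly on the group comparisons. On its most natural reading, over all tests done, the error rate stays below .05. This stands: the defect is an undefined family, not a demonstrated inflation.

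A reader might also infer that the NNNS brings 26 primary tests, since it is "which is conducted twice, once at 36 weeks (± 1 week) PMA and again at 40 weeks (± 1 week"), and that EEG coherence is a candidate. Neither holds. Table 1 places the NNNS at term, the stated comparison intervals do not include 36 weeks, and the primary hypothesis is EEG power. EEG at term and Bayley-III at 18 months are likewise fixed visits. Among the instruments discussed here, the clear open visit is ASQ.

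A further reply is that an article condenses the full protocol, and that EEG band, region and the mechanics of Bonferroni belong in an analysis plan. That is fair for processing detail. It does not cover what the article itself states: primary outcomes set at instrument level, a powered score labelled as only an example, and single-test power beside a promise of multiplicity correction.

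Finally, the powers above are for one specified difference on one score. The chance that some score in a battery reaches significance would be higher, but that would not tell the reader which claim the trial was designed to test.

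**Conclusion.** The concern holds in this limited form. The primary outcomes are named as instruments, no deciding score is chosen for the NNNS, Bayley-III or EEG power, ASQ lacks a visit, and the Bonferroni family is unstated. What follows depends on a choice the plan leaves open. Correction across four instruments gives a joint false-positive chance of about 0.17 (0.11 to 0.19). Correction over every score keeps error below .05 but takes Bayley-III power at 156 retained to 40% at .05/13 and about 31% at .05/28. Table 1 allows for neither.

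The error rates rest on assumed correlations, independence between instruments, one EEG measure and the assumed .05/4 reading. They leave out the preschool language scale, ASQ and cortisol. The powers rest on Table 1's differences and SDs and on 40% attrition, with no allowance for twins. The reproduction of Table 1 as single unadjusted tests needs none of the assumptions about correlation or family.

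**What to change.** In Primary and Secondary Outcome Measures, name one deciding score and visit per primary instrument, preferably the quantity Table 1 already powers:

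- EEG power at term, with its band and region.
- One NNNS score at term: either non-optimal reflexes, with the footnote amended to say so, or another that the sponsor chooses and powers.
- One Bayley-III score at 18 months.

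Assign the preschool language scale, ASQ, HRV and cortisol explicitly to the primary family, each with a score and visit, or to secondary status. HRV needs particular care, because Table 1 powers it at term while the primary list places it at 4 months. State that the between-group comparison at the named visit decides, and that repeated measures ANOVA and all other scores are supportive or exploratory.

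In Planned analyses, replace Bonferroni with Holm's step-down procedure over that named family. It gives the same error control and is never less powerful.

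Restate Table 1 at the adjusted alpha. For three contrasts, the powers at .05/3 with 156 retained are about 68%, 88% and 60%. These are floors under Holm, since its later steps use a larger alpha.

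The cost is wording, made before the final group comparisons, with no new data. Effects on scores that were not nominated could no longer be claimed as primary, and the stated power would be less favourable; keeping the present target means accepting that openly.

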Mothers complete initial assessments after consent and families are then assigned to the FNI intervention group or the SC group using a randomized block design. For randomization, six group assignment cards (3 FNI: 3 SC) are placed in envelopes and sealed. The envelopes are shuffled, numbered and placed in a packet prior to use. The RA withdraws an envelope from the packet to determine group assignment. Within 1 to 2 days of consenting, mothers assigned to the FNI group meet with a Nurture Specialist (NS) designated to facilitate the intervention and begin to carry this out, as described in the Intervention Methods section below. Mothers of infants assigned to the SC condition receive NICU standard care as described in the Standard Care section below. Twins are "clustered" for purposes of randomization, with both infants being assigned to the same group along with the mother.

To determine the total sample size necessary to ensure statistical power of not less than 0.8 to detect differences between group means, we considered the detectable difference for each of the primary outcome variables that would be of interest for a successful study result. Our experience and that of others suggested that effect sizes within the 'medium' range would be achievable (i.e., 0.4 to 0.6). Therefore, given the two independent samples created within the RCT design, assuming a significance level of α = .05 for a two-tailed test, we estimate that we will have at least 80% power (1-*β *≥ .80) to detect a difference between groups for effect sizes and total sample sizes as described in Table 1. Experience with the pilot study suggests that we could expect attrition at a rate as high as 40%. To accommodate this, we intend to recruit a total of N = 260 participants from which a final sample size sufficient to detect all differences of interest should be achieved.

**Table 1 T1:** Power analysis

Outcome Measure	PMA	Reference Population *μ *(*σ*)	Detectable Difference |*μ*_FN_-*μ*_SC_|	Effect Size *d*	Total N Required

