##### Self-report assessments by mothers

Mothers in the two groups read and respond to self-report questionnaires independently and receive advice and consultation that may reduce anxiety and distress. However, it is not possible to blind mothers to group assignment because mothers in the intervention group are given extensive instruction in nurture activities and are given personal attention by the NS. In the course of receiving normal NICU care and attention, mothers in the SC group may observe FNI mothers receiving supplementary attention. Moreover, the infants in the two groups may occupy nearby isolettes. Thus, SC mothers may interact with FNI mothers and observe the FNI activities.

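### The infant 4-month stress response is a primary outcome in one section and a secondary hypothesis in another, and Table 1 gives no power calculation for four of the seven named primary measures

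*Protocol article*

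**What the plan says.** Methods and Design states the primary hypotheses as "increased infant brain activity as assessed by electroencephalogram (EEG) power and better basic neurobehavioral function close to term and at 18 months CA". It then continues: "Our secondary hypotheses are that the FNI group will have decreased stress responses in mother and infant at four months CA".

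Primary and Secondary Outcome Measures gives a longer primary list. After EEG at term it names "infant neurobehavioral function from response to NNNS [62], preschool language scale [78], ASQ [68] and at 18 months CA by Bayley-III Scale [69", and closes with "and the stress response at 4 months CA in infants, as measured by heart rate variability (HRV) and cortisol levels". Its next paragraph, on secondary outcomes, says: "Mother-infant stress responses will be evaluated by cortisol level assessment and autonomic function recordings (HRV, respiratory rate, body temperature".

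The sample-size text under Participants describes the scope of the power analysis in these terms: "we considered the detectable difference for each of the primary outcome variables". Table 1 follows. Its infant rows are EEG (term), NNNS (term), HRV (term) and Bayley-III (18 months). Its mother rows are cortisol (4 months) and CES-D (4 months).

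Table 2 schedules PLS-5 at 24 months only and ASQ at 4, 12, 18 and 24 months. Physiological Assessments confirms that HRV is recorded at the 4-month visit and salivary cortisol during the 4-month session.

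**The concern.** The set of primary outcomes decides what the trial may claim as its main result. Here two sections define that set differently. If infant HRV or cortisol at 4 months favoured the intervention, the outcomes section would support calling it a primary finding. If it did not, Methods and Design would support calling it secondary. Neither report would depart from the published text.

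The power statement adds to the difficulty. It claims to cover each primary variable, but Table 1 matches neither list fully: it leaves out several measures called primary and includes rows that no section calls primary. A reader cannot use Table 1 to settle which list was meant.

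**Working it through.** **Step 1. Compare each measure named primary in the outcomes section with the other sections.**

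| Measure | Within the primary hypotheses in Methods and Design? | Matching row in Table 1? |
|---|---|---|
| EEG at term | Yes | Yes |
| NNNS | Yes (neurobehavioural function near term) | Yes, term |
| Bayley-III, 18 months | Yes | Yes |
| ASQ | At 18 months it can be read as fitting; not named | No |
| PLS | No; Table 2 has 24 months only | No |
| Infant HRV, 4 months | No; listed as secondary | No; HRV row is at term |
| Infant cortisol, 4 months | No; listed as secondary | No; cortisol row is for mothers |

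Three of seven measures have a row; 7 − 3 = 4 do not. Three measures (infant HRV, infant cortisol and PLS) fall outside the primary hypotheses in Methods and Design.

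**Step 2. Reproduce the only HRV figure.** Inputs from Table 1 and the sample-size text: difference 0.5, SD 1.10, two-sided α = .05, power .80, 1:1 allocation.

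- d = 0.5 / 1.10 = 0.4545.
- Normal approximation: n per group = 2(1.960 + 0.842)² / d² = 15.70 / 0.2066 = 76.0, total 152.
- Noncentral t: total 154, which is the printed figure.

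The same t calculation returns the printed totals for EEG (0.2/.434, 150), NNNS (1.0/1.73, 96) and Bayley-III (6/14, 174). The HRV row is therefore correct arithmetic, but for the term assessment.

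**Step 3. Ask whether the missing rows can be filled.** They cannot be filled from the document, which gives no SD and no target difference for infant HRV or infant cortisol at 4 months, PLS or ASQ. As an illustration only, take the article's own range of effect sizes, 0.4 to 0.6. The total N for 80% power is then 200 at d = 0.40 and 90 at d = 0.60. Attrition of 40% leaves 260 × 0.6 = 156. Power with 156 at unadjusted α = .05 is about 70% at d = 0.40, 80% at d = 0.45 and 96% at d = 0.60.

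**Step 4. Show how the choice of list could matter under Bonferroni.** Planned analyses applies the correction but does not say to which family. Suppose, as an assumption, that the divisor were 3 (EEG, NNNS, Bayley-III) or 7 (the measures in the table above), with one test each. For EEG at d = .46 (noncentral t):

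| Total N | α = .05/3 = .0167 | α = .05/7 = .0071 |
|---|---|---|
| 156 (40% attrition) | 67% | 56% |
| 260 (no attrition) | 90% | 84% |

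**The case against.** The best defence is that Methods and Design states constructs and the outcomes section supplies the instruments. On that reading ASQ raises no conflict, because it is given at 18 months and can count as neurobehavioural function. This stands. It does not rescue PLS, which has no 18-month assessment, or the stress response, which Methods and Design names and places in the secondary tier. The secondary paragraph on stress could be read as concerning the mother-infant pair rather than the infant alone. That would soften the overlap within the outcomes section, but Methods and Design names the infant as well as the mother.

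Several stronger readings are tempting but unsupported:

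- *The 4-month endpoints are underpowered.* The article only omits the calculation. Step 3 shows that power could be adequate or not, depending on an effect size that is not given.
- *Power for EEG falls to a definite lower figure.* The divisors 3 and 7 are assumptions. NNNS has 13 subscales and Bayley-III four, so no test count follows from either section, and defining the family may be left to an analysis plan that is not shown.
- *ASQ is biased in favour of the intervention.* The article concedes of self-report that "it is not possible to blind mothers to group assignment" and separates maternal questionnaires from its blinded assessments. The direction of any bias is not shown: mothers taught about normal development might report more delays, not fewer.
- *The cortisol schedule is in real doubt.* Face-to-Face Interactions says "Cortisol is measured at 3, 12, 18 and 24 months CA", but it is describing the 4-month session, and Table 2 and the Figure 3 legend both have 4 months. This is a clerical slip.

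The article also undertakes, under Potential limitations, not to report outcomes selectively. That commitment is welcome, but it cannot be checked while two primary lists exist.

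**Conclusion.** The contradiction holds on the text alone. Infant HRV and cortisol at 4 months are primary in the outcomes section and secondary in Methods and Design, and PLS is primary at an age outside the primary hypotheses. The statement that power was considered for each primary variable is not borne out for four of the seven measures listed. The count of seven takes each named instrument or signal as one measure.

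No claim is made that power is too low for any of the four, and the Bonferroni figures are illustrative. A separate analysis plan could define the multiplicity family, but the two sections of this article would still disagree. Because the status of a result could be settled after it is seen, this should be corrected before group comparisons are made.

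**What to change.** State one primary set, in the same terms, in Methods and Design and in Primary and Secondary Outcome Measures, before any group comparison.

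The simplest repair follows Methods and Design and the infant rows of Table 1 that match it: EEG at term, NNNS near term and Bayley-III at 18 months. Move infant 4-month HRV and cortisol, and PLS, to secondary. Move ASQ as well, unless it is kept as a named 18-month primary with its unblinded maternal report acknowledged. Mark the Table 1 rows for HRV at term, maternal cortisol and CES-D as not primary.

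The sponsor may instead keep the longer list. In that case, change Methods and Design to agree, and reword the sample-size text so that it no longer claims a calculation for every primary outcome.

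Correct 3 to 4 months in the cortisol sentence of Face-to-Face Interactions.

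The cost is wording; data collection does not change. The drawback of the simplest repair is that three measures, or four with ASQ, lose primary status.
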